## Abstract

**Background:**

Loss of control eating (LOC-E) in youth predicts the later development of full-syndrome binge-eating disorder (BED), and therefore, could be a relevant target for prevention treatments. To develop these treatments, it is important to understand the underlying disease processes and mechanisms. Based on the putative role of neurocognitive impairments in the pathogenesis of LOC-E, treatments that modulate these neurocognitive factors warrant further exploration. For instance, stimulants are an effective treatment for impulsivity in youth with attention deficit/hyperactivity disorder (ADHD) and have been shown to improve symptoms of BED in adults. Notably, stimulants have not been examined as a treatment for LOC-E in youth. To explore this gap, we aim to measure change in LOC-E episodes and secondary outcomes in youth with comorbid ADHD and LOC-E who are being started on stimulants.

**Methods:**

We will collect prospective observational data on forty 8-to-13-year-old youth diagnosed with comorbid ADHD and LOC-E who are initiating a stimulant for ADHD. Prior to stimulant initiation, participants will complete baseline measures including LOC-E episode frequency in the last 3 months (primary outcome), and secondary outcomes including disordered eating cognitions, emotions and behaviors, ADHD symptom severity, parental LOC-E, impulsivity and reward sensitivity, and anxiety/mood severity. Outcome measurements will be gathered again at 3-months after initiating the stimulant. Within-patient standardized effect sizes with 95% confidence intervals will be calculated from baseline to 3-month follow-up for all outcomes.

**Discussion:**

Many individuals with LOC-E or binge eating do not fully remit over the course of psychotherapy. Whereas psychotherapy may address psychological and sociocultural domains associated with LOC-E, some individuals with neurocognitive impairments (e.g., ADHD) and neurobiological deficits (e.g., low intrasynaptic dopamine or norepinephrine) may benefit from adjunctive treatment that targets those factors. This will be the first study to provide pilot data for future studies that could examine both the effect of stimulants on LOC-E in youth and underlying mechanisms.

**Trial registration:**

Trial registration number: NCT05592119

## Background

Binge-eating episodes are defined as the consumption of an objectively large amount of food while experiencing a loss of control over eating [1]. In children, accurately quantifying a “large amount of food” is problematic because intermittent overconsumption is a normal behavior in growing youth [2]. Instead, many researchers measure ‘loss of control eating’ (LOC-E) rather than binge eating when studying disordered eating in youth. Notably, 9–30% of 9–13-year-old youth experience LOC-E, though only 1/3 to 1/2 of these children present with these symptoms after 5 years [3]. In addition to a high prevalence rate, LOC-E in middle childhood (8–12 years old) also robustly predicts the later development of partial or full-syndrome binge-eating disorder (BED) [4–6] and excessive weight gain in children at high risk for adult obesity [4, 7]. Based on these factors, LOC-E has been proposed as a relevant target for preventive interventions [8].

To develop treatments for LOC-E, it is important to understand the underlying disease processes and mechanisms. Recent evidence suggests that neurocognitive predisposing factors (e.g., impulsivity and dysfunctional reward processing) are relevant in the pathogenesis of LOC-E. First, there is evidence that children (8–14 years old) with Attention Deficit/Hyperactivity Disorder (ADHD) have 12 times the risk of experiencing LOC-E compared to healthy controls [9]. This study also found that children with LOC-E are more likely to exhibit high impulsivity on a neurobehavioral task (*Go/No Go*) and parent-rated scale compared to healthy controls. Another study used a delay of gratification task (DoGT) in children with ADHD or LOC-E, comorbid diagnoses (ADHD and LOC-E), and healthy controls [10]. They found that children with ADHD and comorbid diagnoses had significantly higher risk of eating prematurely during the DoGT compared to children with only LOC-E or healthy controls. Moreover, the children with comorbid diagnoses were most likely to worry about losing control over eating during the task. These findings suggest that a lack of behavioral inhibition (to food reward) in children with ADHD is a relevant factor in the drive to eat prematurely [10].

Neurobiological studies have shown that the relationship between ADHD and binge eating (in adults) is largely explained by shared genetic risk factors [11]; however, there are also non-shared environmental factors that explain the covariance [8]. In a neuroimaging study, Murray et al. [12] found that children with early onset BED have underlying dysconnectivity between the brain’s inhibitory network and reward system. These findings suggest that poor connectivity between reward and impulse-control-related neural pathways underlie some children’s inability to regulate their drive to eat. Importantly, similar perturbations in functional connectivity have been illustrated in key nodes of the inhibitory control network in those with ADHD [13] – suggesting similar underlying mechanisms.

Recent research has started to delineate not only the association between ADHD and LOC-E, but also the directionality of the relationship. A large longitudinal study by Sonneville et al. [14] showed that ADHD in children (mean = 11.7 years old) predicted binge eating in mid-adolescence (14–16 years old) via late childhood overeating and early adolescent ‘strong desire for food’. Relatedly, emerging longitudinal data are supporting a causal role of ADHD in contributing to excessive weight gain [15].

Considering this evidence, it is relevant to examine whether modifying neurocognitive symptoms, such as impulsivity, influences LOC-E and the subsequent development of eating disorders and obesity. Stimulant medication is an example of a treatment that could modify these neurocognitive symptoms, and in doing so, potentially effect change in symptoms of LOC-E. Robust evidence supports stimulants as an efficacious treatment for impulsivity in youth with ADHD [16]; however, studies have not explored the effect of stimulants on LOC-E in children. Relevantly though, there is evidence that stimulants improve symptoms of binge eating in adults, and also, that stimulants may mediate this effect by improving impulsivity [17–19]. Notably, the stimulant lisdexamfetamine (LDX) received regulatory approval for the treatment of moderate to severe BED in adults based on one 11-week Phase 2 dose-finding study and two identically designed 12-week Phase 3 dose optimization studies [19–21]. Across the Phase 3 trials, LDX (50 and 70 mg/day) was superior to placebo in decreasing binge eating days/week and improving key secondary outcomes (e.g., binge cessation) over 12-weeks [19].

In addition to clinical trial evidence, there are also neurobiological studies that support the use of stimulants as a treatment for LOC-E [22, 23]. For example, explanatory models for ADHD suggest that reduced dopamine neuronal tone affects executive functioning and reward processing [24]. Similarly, disordered eating, such as binge eating has been associated with lower dopamine (and norepinephrine) metabolite levels in the cerebrospinal fluid [25, 26]. In sum, for ADHD and eating disorders, there is evidence of altered dopaminergic tone, presumably *lower* intrasynaptic dopamine, and since stimulant medications *increase* intrasynaptic dopamine and norepinephrine levels in striatal and cortical brain regions, a plausible explanatory model supports the use of stimulant medication for LOC-E.

As further support for exploring the effect of stimulants on LOC-E in youth, retrospective and cross-sectional data suggests that children with ADHD who had been treated with stimulants had less odds of obesity compared to those who were not medicated [27]. Importantly, the research does not elucidate whether stimulants were associated with lower obesity rates because they lessened symptoms of LOC-E, or alternatively, whether a different mechanism mediated the apparent effect on obesity (e.g., appetite suppression independent of effect on disordered eating).

In sum, though stimulants warrant investigation as a treatment for LOC-E in youth, no studies have prospectively examined the effect of stimulants on this form of disordered eating. To gather pilot data, we aim to measure prospective, observational outcomes in a clinical setting to examine the effect of stimulant initiation on LOC-E in children with comorbid ADHD and LOC-E. We will also collect exploratory secondary outcomes to measure eating-related cognitions, emotions and behaviors, ADHD symptom severity, parental LOC-E, impulsivity and reward sensitivity, and anxiety/mood symptoms. Given the observational design, we will not generate a priori hypotheses.

## Methods

### Design

This study will use a prospective, observational case series design. Ethics approval was obtained through the Nova Scotia Health Research Ethics Board.

### Participants

We will collect data on forty 8–13-year-old youth and their parents. The study will use a prospective cohort sample from the Atlantic ADHD Centre in Dartmouth, Nova Scotia. To be eligible for inclusion, youth must (A) meet the diagnostic criteria for ADHD, and (B) have experienced at least 3 episodes of LOC-E during the past 3 months^1^, accompanied by some degree of distress and 2 of the 5 behavioral symptoms associated with LOC-E. Inherent to the definition of LOC-E, consumption of an abnormally large amount of food will not be required. Further details related to the diagnostic assessment for ADHD and LOC-E are provided in later sections. Participants will be excluded if they are (a) currently receiving psychotherapy treatments for ADHD, eating disorders, or obesity, and/or (b) undergoing concurrent medication changes that could affect ADHD or eating related symptoms (as determined by psychiatrist and principal investigator [[name]]). Participants must also have sufficient language skills and a general practitioner to initiate the stimulant and monitor adverse events.

### Measures

The following outcome measures will be collected at various time points including the pre-screening visit, screening visit, baseline, and 3-month follow-up. Figure 1 illustrates an overview of these study visits.

**Fig. 1 Fig1:**
[figure not shown]
Timeline of Study Procedures. *CPT* Continuous Performance Test. *CBBEQ* Children’s Brief Binge-Eating Questionnaire. *ChEDE* Eating Disorder Examination – Child Version. *ChEDE-Q8* Eating Disorder Examination Questionnaire adapted for children, short form. *CEBQ* Child Eating Behavior Questionnaire. *LOCES* Loss of Control Over Eating Scale. *RCADS-25* Revised Child Anxiety and Depression Scale – Short Version. *VADPRS* Vanderblit ADHD Diagnostic Parent Rating Scale. *BIS/BAS* Parent-Report Behavioral Inhibition System/Behavioral Activation System Scales

#### Children’s brief binge-eating Questionnaire (CBBEQ)

The CBBEQ is a 7-item screening tool for binge-eating symptomatology that has been validated for use with children aged 7 and above [29]. In this self-report measure, level of agreement with statements concerning eating behaviors and thoughts regarding food are rated on a 4-point Likert scale from 0 (definitely false) to 3 (definitely true). The global mean score of the CBBEQ will be used, with higher scores indicating greater levels of global binge-eating symptomatology. The CBBEQ has high internal consistency and concurrent validity, and scores above 8 warrant a more extensive interview for diagnostic assessment [29].

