### Procedure

Clinicians at the ADHD clinic will routinely pre-screen for LOC-E, using the CBBEQ [29], as part of their standard clinical assessment (see Fig. 1 for schedule of assessments). The clinic’s standard ADHD diagnostic assessment includes a psychiatric history by an ADHD expert (JS) and cognitive data using a validated Continuous Performance Test (CPT). Patients who are diagnosed with ADHD and pre-screen positive for LOC-E (score of 8 or above on the CBBEQ), and who receive a recommendation to start a stimulant medication and intend to initiate the stimulant, will be invited to the consent and screening visit. Pre-screening data collection is standard practice at the clinic (i.e., relevant personal health information and scale-based outcomes) and will not be recorded for the study as consent will not have been obtained. However, clinic staff will record the following non-personal health information that can be used in a participant flow diagram for study purposes: (a) number of positive and negative pre-screens, and (b) number of patients who are interested or not interested in being contacted by a research staff to learn more about the study.

Parents and children who are interested in participating will meet with a research assistant over Zoom for Healthcare to review the consent form and undergo a more detailed screening visit to establish eligibility. During the screening visit a trained research assistant will use the diagnostic version of the ChEDE to confirm the LOC-E inclusion criteria are met. If the LOC-E diagnosis is confirmed and no exclusion criteria are met, the child’s parent will be instructed to contact the research assistant approximately 2 weeks prior to stimulant initiation (which will occur naturalistically in the child’s physician’s office outside of the study context). At that time, participants will meet with a research assistant again to obtain baseline measurements (i.e., prior to stimulant initiation) and demographic information (age, sex, previous and current psychological and pharmacological treatments, and parent reported comorbid diagnoses of physical and psychiatric conditions). Outcome measurements will be gathered again at 3-months after initiating the stimulant, as will information about the stimulant treatment (i.e., type, dose, adherence, and adverse events [adapted from the Pittsburgh Side-Effects Rating Scale]) [52]. Participants will be paid $25 per visit after the final study visit.

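### The CBBEQ is to be scored as a global mean, which cannot exceed 3, but the pre-screen cut-off is 8; the cut-off is also worded in two ways that disagree at exactly 8

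*Protocol article*

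**What the plan says.** The protocol article deals with the Children's Brief Binge-Eating Questionnaire (CBBEQ) in two places.

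- **Measures, CBBEQ section.** "The CBBEQ is a 7-item screening tool for binge-eating symptomatology", with statements "rated on a 4-point Likert scale from 0 (definitely false) to 3 (definitely true"). On scoring: "The global mean score of the CBBEQ will be used, with higher scores indicating greater levels of global binge-eating symptomatology". On the threshold, citing the validation source: "scores above 8 warrant a more extensive interview for diagnostic assessment".
- **Procedure.** "Clinicians at the ADHD clinic will routinely pre-screen for LOC-E, using the CBBEQ", as part of the usual clinical assessment. Among the conditions for an invitation to the consent and screening visit, the patient must "pre-screen positive for LOC-E (score of 8 or above on the CBBEQ"). At that visit, "a trained research assistant will use the diagnostic version of the ChEDE to confirm the LOC-E inclusion criteria are met".

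Procedure adds that pre-screening data "will not be recorded for the study as consent will not have been obtained". Clinic staff keep only non-personal counts for a participant flow diagram, including the numbers of positive and negative pre-screens. The CBBEQ does not appear under Primary outcome or Secondary outcomes, so pre-screening is the only use the article gives it.

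**The concern.** A scoring rule and a decision threshold have to be on the same scale. Here the rule yields a number no larger than 3 and the threshold is 8. Nowhere does the article say that the threshold applies to a sum.

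The phrase is hard to read as a loose synonym for a total, because the article uses both terms. It specifies total scores for the VADPRS and BIS/BAS subscales, and a global mean for the ChEDE-Q8, the CEBQ and the LOCES. A reader would take the CBBEQ instruction in the same literal sense.

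The threshold also has two forms, one strict and one inclusive, and no departure from the validation source is explained.

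What is at stake is the step that decides who is invited. The later ChEDE interview can remove children wrongly invited, but it cannot recover children wrongly left out, because they never reach it. Since CBBEQ scores are not kept for the study, a misapplied rule could not be traced from study data. The counts of positive and negative pre-screens depend directly on the rule used.

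**Working it through.** **Inputs, all from the protocol article**

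- Number of items: 7 (CBBEQ section)
- Item range: 0 to 3 (CBBEQ section)
- Scoring rule: global mean (CBBEQ section)
- Threshold in the CBBEQ section: above 8 (citing the validation source)
- Threshold under Procedure: 8 or above (the study's own rule)

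**Step 1. Can the stated threshold be reached with the stated score?**

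- Mean: minimum 7 × 0 / 7 = 0; maximum 7 × 3 / 7 = 3. Since 3 < 8, neither wording can be met.
- Sum: minimum 7 × 0 = 0; maximum 7 × 3 = 21. Since 21 > 8, both wordings can be met.

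Full enumeration of the 4^7 = 16,384 possible response patterns agrees: none has a mean of 8 or more. The threshold cannot be reproduced on the mean scale and makes sense only for the sum. On the mean scale, a sum of 8 would be 8/7 = 1.14 and a sum of 9 would be 9/7 = 1.29.

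**Step 2. Do the two wordings agree once the sum is used?**

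The sum is an integer, so above 8 means 9 or more.

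| Sum | Above 8 | 8 or above |
|---|---|---|
| 7 or less | negative | negative |
| exactly 8 | negative | positive |
| 9 or more | positive | positive |

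Of the 16,384 patterns, 13,792 have a sum of 8 or more and 12,238 have a sum above 8. The difference, 13,792 − 12,238 = 1,554, is the number of patterns with a sum of exactly 8. These count possible answer sheets and do not estimate the share of patients. The article gives no score distribution, so the proportion of children at exactly 8 is unknown.

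**Step 3. Where does the score go afterwards?**

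The primary outcome is LOC-E episode frequency from the ChEDE, and the CBBEQ is not a secondary outcome. The Data analytic plan computes within-patient change in the listed outcomes. No CBBEQ score enters an estimate; the score acts only through who is invited and through the pre-screen counts.

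**The case against.** The strongest reply is that nobody would apply the mean. The rule under Procedure refers simply to a score and never mentions a mean. A threshold of 8 on seven 0–3 items can only be a sum, clinicians already use the tool routinely, and an unreachable cut-off would show itself with the first child scored. This stands as an argument about consequences. A reader might infer that recruitment would be zero. That follows only from a literal reading, and the documents do not support it as a realistic outcome. The text still needs correcting, because a team following the CBBEQ section could not reproduce the pre-screen.

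A second reply is that the two boundaries have different jobs: the CBBEQ section reports what the validation source recommends, and Procedure alone sets the study's rule. This also stands in part. Procedure defines a positive pre-screen, so it would go too far to call the flow-diagram counts uninterpretable. But the article cites the same source for the tool in both places and does not say that it departs from it, so the mismatch at exactly 8 remains unexplained.

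A reader might also see a contradiction between a score that will be used and pre-screening data that "will not be recorded for the study as consent will not have been obtained". There is none. A score can decide whom to invite without being kept as study data, and Procedure gives the reason.

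Finally, it is tempting to say that the inclusive boundary is harmless because it adds only a few ChEDE interviews. The article gives neither referral volumes nor a score distribution, so that cannot be claimed.

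**Conclusion.** The point holds on two counts. First, the scoring rule in the CBBEQ section is incompatible with the cut-off of 8: the largest possible mean is 3, and only the sum, with its maximum of 21, reaches 8. Second, the two wordings of the cut-off classify a child with a sum of exactly 8 differently. Both follow from the article's own figures, with no assumption beyond integer item scores and complete responses.

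The practical weight is modest. Staff would in all likelihood sum the items, Procedure states one operating rule, eligibility rests on the ChEDE, and the effect estimates could be touched only through the make-up of the sample. The remaining effect is on whether children scoring exactly 8 are invited and on how the pre-screen counts are read. Its size cannot be given from the documents, nor can they show which boundary the validation source supports.

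**What to change.** 1. In the CBBEQ section, replace the reference to a global mean with: total score (sum of 7 items, range 0–21).
2. Check the cut-off against the cited validation source, then use one boundary, worded identically, in the CBBEQ section and under Procedure. If the study's rule is meant to differ from the source, say so and give the reason.
3. Report the scoring and boundary actually applied alongside the pre-screen counts in the flow diagram.

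The cost is a wording correction and a short note to clinic staff. No outcome, visit or analysis changes.

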#### Vanderbilt ADHD diagnostic parent rating scale (VADPRS)

The VADPRS [30], which is to be completed by the parent of the child under assessment, is a 56-item measure used to evaluate ADHD behaviors, along with academic and social performance in children aged 6 and above. The VADPRS incorporates all DSM-5 criteria for both ADHD subtypes [31], and is divided into two components: one which specifically assesses ADHD symptoms, and the other examines impairment in performance. The ADHD symptoms component consists of two ADHD subscales, inattention and hyperactivity/impulsivity, as well as three subscales for common comorbidities, including oppositional defiant disorder, conduct disorder, and anxiety/depression. Scores range from 0 (never) to 3 (very often) on a 4-point Likert scale, with higher scores indicating greater levels of symptoms exhibited by the child. The performance component has scores ranging from 1 (excellent) to 5 (problematic) on a 5-point scale, with higher scores indicating greater impairment in academic and/or social performance. The total scores from each subscale of the symptomatology component will be used in combination with the score of the impairment in performance component. The VADPRS has demonstrated good construct, discriminant, and content validity, as well as internal consistency [30, 32–34].

#### Eating disorder examination – child Version 17.D/C.1 (ChEDE) – diagnostic item 11

The EDE 17.0D [35], which measures eating disorder symptom severity, has been adapted for use with children ages 8 and above [36, 37]. The ChEDE has been shown to have high inter-rater reliability and internal consistency [38, 39]. For the purposes of this study, only diagnostic item 11 (identifying bulimic episodes and other episodes of overeating) of the ChEDE will be used, which includes questions regarding feelings of loss of control over eating, features associated with binge eating, and distress about binge eating. The measure will be used for diagnostic assessment of LOC-E for study inclusion purposes, and at a baseline and 3-month follow-up to establish LOC-E episode frequency. The ChEDE will be administered by well trained research assistants tasked to develop positive rapport with the children and ensure concepts are explained in a manner that is developmentally appropriate to each child [see 40 for a detailed description]. Also, parents will remain present during the assessment in case the children need assistance understanding the interviewer.

